### Interim analyses {21b}

There are no intentions for an interim analysis. This decision is grounded in three key reasons: first, the OMIs is extensively utilized and has demonstrated a reliable safety record, leading us to conclude that interim analyses to affirm safety may be unnecessary. Second, our study employs a blinded design, eliminating the anticipation of disclosing data allocation status prior to analysis, where interim analyses could potentially compromise the design’s integrity. Last, from a statistical perspective, interim analyses carry the risk of generating false positives. In the absence of adequate statistical adjustments, regular examination of the data could yield misleading insights.

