Additional support for the efficacy of OMIs comes from Aguilar-Rodríguez et al.,  who found that such interventions accelerate the progression to full oral feeding and shorten hospital stays [10]. Systematic and meta-analysis reinforce this conclusion, establishing OMIs as an efficacious strategy for bolstering oral feeding in preterm infants [11–14]. Lv et al.’s work underscores the positive effect of early motor interventions on oral feeding ability of preterm infants [15]. Similarly, Wu et al. concluded that oral massage not only improves sucking efficiency but also diminishes the risk of adverse events such as infections and apnea [16]. Wang et al. further validate that OMIs improved feeding performance in preterm infants and did not increase the occurrence of complications associated with prematurity [17]. Thus, integrating OMIs in NICU presents several significant clinical benefits, including: (1) improving oral feeding skills and reducing the transition period from tube feeding or parenteral nutrition to full oral feeding, thereby increasing feeding efficiency; (2) improving the quality of survival by reducing hospitalization durations; and (3) providing early sensory stimulation to support neurobehavioral development in preterm infants.

Despite these advancements, establishing a standardized timing for initiating OMIs remains elusive. Diverse studies advocate different start times, ranging from the infant’s first day following admission [17] to 48 h after ceasing non-invasive ventilation [18, 19], or at the onset of feeding [15]. The cumulative effects of these divergent starting points remain nebulous, compounded by the lack of long-term follow-up research that would elucidate their extended impacts. Consequently, the primary objective of this study is to compare the effects of different initiation times for OMIs on the feeding progress among preterm infants. Simultaneously, it endeavors to evaluate the long-term outcomes of OMIs on both feeding efficiency and neurodevelopment outcomes in preterm infants.

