#### Recruitment {15}

Recruitment is currently in progress. We estimate an average enrollment of 12 participants per month based on the anticipated number of preterm admitted to the NICU and recruitment rates observed in our previous pilot studies. The research team will maintain daily checks of the electronic medical record system and communicate with the clinical team to identify infants who potentially meet the eligibility criteria, along with their parents. The research nurse will approach the eligible infants' parents, provide them with information, and obtain their consent.

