### Procedure for unblinding if needed {17b}

We do not expect the need to reveal the data’s allocation status before conducting the analyses.

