### Composition of the data monitoring committee, its role, and reporting structure {21a}

A data safety monitoring committee will be instituted, comprised of three professionals with specialized knowledge in neonatology and nursing. These committee members will be maintained independent from the investigators, ensuring there are no scientific, financial, or other conflicts of interest with the study. Furthermore, the committee is tasked with safeguarding the authenticity and integrity of the data, ensuring that the study’s findings are reliable and credible.

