### Frequency and plans for auditing trial conduct {23}

The trial steering committee, the quality control team alongside the data monitoring and ethics committee will convene biannually to scrutinize several key areas: fidelity to the research trial’s protocol, the data’s accuracy and integrity, adherence to ethical guidelines, effective execution of safety reporting and monitoring protocols for participants, swift recognition and resolution of potential safety concerns, and the trial’s compliance with applicable national and international regulations, guidelines, and standards.

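### No comparison of adverse event rates between the arms is planned during enrolment, although the twice-yearly committee meetings are expected to recognise safety concerns swiftly

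*Protocol article*

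**What the plan says.** All references are to the protocol article.

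- **Interim analyses {21b}:** "There are no intentions for an interim analysis". Three reasons follow. OMIs are widely used with a good safety record, "leading us to conclude that interim analyses to affirm safety may be unnecessary". The design is blinded, "eliminating the anticipation of disclosing data allocation status prior to analysis". Repeated looks without adjustment can produce false positives.
- **Procedure for unblinding {17b}:** the team does not expect to need to reveal "allocation status before conducting the analyses". No exception is stated for the committee.
- **Composition of the data monitoring committee {21a}:** three members, independent of the investigators, under the name of a data safety monitoring committee. The one task written there is that "the committee is tasked with safeguarding the authenticity and integrity of the data".
- **Frequency and plans for auditing {23}:** the steering committee, the quality control team and the data monitoring and ethics committee meet twice a year. Their agenda includes "swift recognition and resolution of potential safety concerns". Whether safety data are shown pooled or by arm is not stated.
- **Who will be blinded {17a}:** participants, families, data collectors and statisticians. Neither the committee nor the nurses who deliver the intervention are listed.
- **Safety indicators (Outcomes {12}):** the rate of adverse events in the intervention period.

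**The concern.** Both arms receive the same OMI programme and differ only in when it starts (Late OMIs group). Eligible infants need non-invasive respiratory support and enrol within 72 h of birth. The early arm starts once milk is given and vital signs are stable; the late arm waits until 48 h after nasal CPAP has stopped. Early-arm infants may therefore be stimulated while still on respiratory support. Whether that raises the rate of desaturation, bradycardia, apnea or aspiration is the safety question the randomisation can answer.

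A body with safety in its name, meeting on a schedule with safety on the agenda, would normally be shown the data that bear on that question. Sections 17b and 21b foresee no release of allocation, and 21b argues against a safety look. If the committee sees only pooled counts or single reports, it cannot tell an excess in one arm from a common background rate in these infants.

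**Working it through.** **1. Do the three reasons in section 21b cover a committee review of harms?**

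| Reason given | Applied to a closed, descriptive review by arm |
|---|---|
| OMIs have a good safety record | Both arms receive OMIs, so a record for OMIs in general does not settle the contrast in start time. The Background offers partial reassurance: one cited study is described as showing no increase in complications of prematurity, and the same reference is linked to a start on the first day after admission. |
| A look would compromise the blind | The committee is independent of the investigators (21a) and is not among the blinded parties (17a). A closed report to it leaves all of those parties blinded. |
| Looks create false positives | This concerns unadjusted testing. A descriptive adverse event table does not test transition time and spends none of its alpha. |

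On the third reason, a simulation of 1,000,000 trials under the null tested one outcome at 72, 144, 216 and 280 infants. The overall type I error is 0.125 if every test uses 0.05, and 0.051 if the three earlier tests use 0.001. The risk is real for unadjusted tests of the primary outcome. It does not arise from a table of harms on which no test is made.

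**2. How many meetings could matter?** Inputs: "We estimate an average enrollment of 12 participants per month" (Recruitment {15}); 280 infants (Sample size {14}); two meetings a year (section 23). First meeting at six months is an assumption.

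- Infants enrolled between meetings: 12 × 6 = 72, and 72/280 = 25.7%.
- The last infant enrols at 280/12 = 23.3 months.
- Meetings at months 6, 12 and 18 fall at 72, 144 and 216 infants, or 36, 72 and 108 per arm. A fourth, at month 24, comes after the last enrolment.

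**3. What do pooled counts hide?** The protocol gives no adverse event rates, so these are assumptions. With 36 per arm and true proportions of 25% (early) and 10% (late), expected counts are 36 × 0.25 = 9 and 36 × 0.10 = 3.6. Pooled, (9 + 3.6)/72 = 17.5%, the same as 17.5% in each arm.

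**4. What would a comparison by arm show?** Approximate power, two-sided 0.05, with p̄ the mean of the two proportions:

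Φ{ [|p₂ − p₁| − 1.96·√(2p̄(1 − p̄)/n)] / √[(p₁(1 − p₁) + p₂(1 − p₂))/n] }

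For 20% versus 40% and n = 36, p̄ = 0.30: (0.200 − 1.96 × 0.1080)/0.1054 = −0.11, so power is 0.456.

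| Assumed proportions | 36 per arm | 72 per arm | 108 per arm |
|---|---|---|---|
| 5% vs 10% | 12% | 21% | 29% |
| 10% vs 20% | 22% | 39% | 54% |
| 20% vs 40% | 46% | 75% | 90% |

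The power figures only gauge how much the table can reveal; no test is proposed. Chance gaps are common early on. At 36 per arm, 9 versus 4 infants with an event gives Fisher p = 0.22. If both arms truly had 17.5%, a gap of five or more in either direction would occur about 16% of the time.

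**5. Is exposure equal?** Events are counted in the intervention period, which ends by the same rule in both arms but starts at different times. Take the planning means of 11.36 and 13.40 days (section 14), read initiation of feeding as first milk, and let L be the days from first milk to the late start. Apart from any common tail of 48 h, the early period averages 11.36 days and the late one 13.40 − L. The early period is longer when L > 13.40 − 11.36 = 2.04 days. The late start is 2 days after CPAP stops, so this holds once CPAP outlasts first milk by more than 0.04 day on average. Raw counts could then show an early-arm excess from exposure alone.

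**The case against.** A reader might infer that the plan forbids any look by arm and that harm from an early start cannot be seen until the trial ends. The documents do not support this. Sections 17b and 21b state intentions and expectations, not a ban, and section 23 leaves open what the committee is shown. Events are documented and reported under continuous monitoring (section 22), a session stops if the infant's condition changes (Early OMIs group), and severe adverse events are a termination criterion (Eligibility criteria). The treating nurses know the arm. These safeguards act on the individual infant; none compares event rates between arms.

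A reader might also take section 21a to confine the committee to data integrity. That is too narrow: its name and section 23 both give it a safety role. The two sections should simply say the same thing.

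Nor should the Background sentence "The cumulative effects of these divergent starting points remain nebulous" be read as a statement about acute harm. It concerns cumulative and longer-term effects, and the cited study linked to a first-day start is some reassurance.

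Finally, closed sessions and the authorship of reports are often left to a committee charter, and their absence from an article is no defect. The point rests instead on a printed decision with printed reasons, set against a printed expectation of swift recognition. The objection that early looks are imprecise and that raw counts are confounded by exposure stands in full, and it shapes the fix.

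**Conclusion.** The point holds in this limited form: as written, the plan provides no comparison of event rates between arms during enrolment, and the reasons in section 21b do not justify withholding one from an independent committee. About three scheduled meetings could use such a comparison. What it would reveal depends on event rates the protocol does not give: a doubling from 20% would probably be noticed by the second or third meeting, while a doubling from 5% would usually be missed at all three. The timing assumes 12 infants per month and meetings every six months from the start. This is a cheap improvement in participant safety. It does not affect the validity of the primary analysis.

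**What to change.** Reconcile sections 17b, 21a, 21b and 23.

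- **21b and 17b:** keep the rule of no interim efficacy analysis. State that, as the one exception to non-disclosure, the independent committee receives a descriptive table of adverse and serious adverse events by arm at each existing twice-yearly meeting, in closed session without the steering committee, the quality control team or the investigators.
- **21a:** state that the remit includes participant safety and advice to the steering committee.
- **Content of the table:** show events per infant and per intervention day, or count them over a common window from first milk in both arms. The common window requires events to be recorded in the late arm before its intervention starts. No hypothesis test is made and no alpha is spent.
- **Preparation:** the independent holder of the randomisation scheme (Concealment mechanism {16b}) can prepare it, provided that person collects no outcome data, so the trial statistician stays blinded.

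Cost: a few sentences of protocol text, a little more work per meeting and, if the common window is chosen, some extra recording in the late arm. Early counts will be small, will show only large excesses, and should be read with caution.

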### Methods for additional analyses (e.g., subgroup analyses) {20b}

The sub-group analysis based on gestational age will be performed. If required, according to the type of variable and their distributions, linear or logistic regressions will be performed. Multivariate regressions will also be conducted for selected outcomes, if necessary. In cases where a baseline characteristic in the enrolled population differs between the two groups with a *P* < 0.05 in the univariate analysis, then the results will be adjusted for that variable).

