#### Sample size {14}

The sample size was calculated using the online calculator available at http://powerandsamplesize.com/, based on the primary outcome measure of transition time—the duration time from the initiation of feeding to achieving full oral feeding. A two-sample independent means comparison method was applied for this calculation. The sample size calculation accounts are based on a type I error probability of 5% and a statistical power of 80%. According to our pilot study (*n* = 26), the mean transition times for the two groups were found to be μ1 = 11.36 days for the early OMIs group, μ2 = 13.40 days for the late OMIs group, with a *σ* = 4.99 days. The two groups were allocated in a 1:1 ratio; the initial calculation indicated a need for 126 participants per group. To account for potential dropouts or exclusions, the sample size was augmented by 10%, resulting in a total of 280 participants, or 140 participants per group.

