### Data management {19}

Establishment of the data monitoring committee to strictly control the data collection. Demographic and background clinical data describing the sample that will be collected from the electronic medical record system will include maternal parity, maternal age, maternal disease, pregnancy complications and co-morbidities, conception method, delivery method, infant GA at birth, infant birth weight, infant height, infant head circumference, infant Apgar scores, infant sex, diagnoses, and so on.

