## Statistical methods

### Statistical methods for primary and secondary outcomes {20a}

The intention-to-treat analysis (ITT) will be the main analysis, with a per-protocol set (PPs) analysis conducted simultaneously. A significance level of *P* < 0.05 will be considered statistically significant. In the ITT analysis, all subjects will be included in the group to which they are assigned, regardless of whether they completely received the intervention. (1) Descriptive statistics will be used to summarize baseline characteristics. Continuous variables will be presented as Mean ± Standard deviation and categorical variables as percentages (%). (2) For comparisons between groups, Student *t*-tests will be applied for continuous variables, and chi-square tests will be utilized for categorical variables. (3) Assessment of efficacy: for continuous variables, independent Student *t*-tests will be employed for evaluation if conditions are met. (4) For data that do not follow a normal distribution, ordinal data, or data with significantly unequal variances, non-parametric tests will be used. The statistical analysis will be conducted using the medical statistical software SPSS 23.0 (SPSS, IBM Corporation, Armonk, NY, USA).

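### Selecting covariates by baseline P<0.05 leaves gestational age unadjusted in about 95% of randomisations, and the non-parametric fallback does not test the mean difference the trial was sized on

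*Protocol article*

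**What the plan says.** Two data-driven rules are written into the protocol article.

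- **Covariates** (Methods for additional analyses {20b}): where a baseline characteristic differs between the groups at P<0.05 "in the univariate analysis, then the results will be adjusted for that variable". Other regressions are optional and name no covariates. Gestational age appears there only as a subgroup factor.
- **Test** (Statistical methods for primary and secondary outcomes {20a}): Student's t-test is used if its conditions hold. For data that are non-normal or ordinal, "or data with significantly unequal variances, non-parametric tests will be used".

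Three other sections bear on these rules.

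- Sequence generation {16a} allocates by odd or even random number, with no stratification.
- Data management {19} lists the baseline variables to be collected, including "infant GA at birth, infant birth weight, infant height, infant head circumference, infant Apgar scores, infant sex".
- Sample size {14} plans for a difference in mean transition time: "A two-sample independent means comparison method was applied for this calculation", with "μ1 = 11.36 days for the early OMIs group, μ2 = 13.40 days for the late OMIs group" and a common SD of 4.99 days.

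**The concern.** After proper randomisation, a significant baseline difference is a chance event. Selecting on it ignores how strongly a variable predicts the outcome. Eligibility runs from 29+0 to 34+6 weeks, and the investigators single out gestational age for a subgroup analysis. Even so, the rule will normally leave it out, while a variable of no prognostic value can enter by luck. The adjustment set is then unknown until the data are seen, and precision available from a variable already collected is given up.

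The test rule raises a different problem. A rank test compares distributions. It addresses the difference in means only under extra conditions, such as a pure shift. Unequal variances, one of the triggers for the fallback, are a sign that those conditions fail. The fallback also gives no estimate in days to set against the planned 2.04 days.

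**Working it through.** **The plan's own figure.** δ = 13.40 − 11.36 = 2.04 days and σ = 4.99 days. With n per arm = 2(z₀.₉₇₅ + z_power)²σ²/δ² and σ²/δ² = 24.90/4.162 = 5.983:

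- 80% power, two-sided 5%: 2 × 7.849 × 5.983 = 93.9, so 94
- 90% power, two-sided 5%: 2 × 10.507 × 5.983 = 125.7, so 126

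The article reports that "the initial calculation indicated a need for 126 participants per group" while stating 80% power. Its 126 corresponds to 90%; a one-sided test at 80% would need 74. That mismatch is a separate point to reconcile. The calculations below use 126 per arm, where unadjusted power is about 0.90.

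**How often the covariate rule acts.** Under unstratified randomisation, any one baseline variable reaches P<0.05 with probability 0.05 (simulated 4.8 to 5.2%). Gestational age is therefore left out under this rule in about 95% of trials. For k independent variables, the chance that at least one enters is 1 − 0.95^k: 0.40 for k = 10 and 0.64 for k = 20. This is only indicative, because the listed variables are correlated and the list is open-ended.

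**What the covariate rule costs.** The unadjusted SE is 4.99 × √(2/126) = 0.629 days. Adjusting for a covariate with correlation r to the outcome multiplies it by √(1 − r²). The article gives no r, so 0.3 to 0.7 is assumed. Simulation used 20,000 runs with normal data:

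| r (assumed) | SE adjusted, days | Power, always adjust | Power, article's rule | Type I error, article's rule |
|---|---|---|---|---|
| 0.3 | 0.600 | 0.926 | 0.904 | 0.048 |
| 0.5 | 0.544 | 0.960 | 0.908 | 0.043 |
| 0.7 | 0.449 | 0.994 | 0.914 | 0.034 |

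By formula, the n per arm for 80% power falls from 94 to 86, 71 and 48.

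**What the test rule does when means are equal.** Assumed here: 126 per arm, both means 12.4 days (about midway between the planning means), and lognormal data. Rejection rates of the article's test rule in 5,000 runs:

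| SDs, days | Rejection rate |
|---|---|
| 4.99 and 4.99 | 5.1% |
| 4.75 and 5.25 | 5.6% |
| 4.5 and 5.5 | 8.5% |
| 4 and 6 | 18.9% |

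Welch's test rejected in 5.8% at equal SDs. In a separate 10,000-run simulation at 4 vs 6, the Mann-Whitney test rejected in 19.9% and Welch in 4.9%. With gamma data the figures were 13.5% and 5.2%. With symmetric normal data at 4 vs 6, Mann-Whitney rejected in only 5.1%.

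The mechanism is that equal means need not imply equal medians. A lognormal median is mean/√(1 + (SD/mean)²). SD 4 gives 12.4/1.051 = 11.80 and SD 6 gives 12.4/1.111 = 11.16, a gap of 0.64 day. SDs of 4.5 and 5.5 give 11.66 and 11.33, a gap of about 0.32 day.

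**Whether the fallback would be triggered.** At SDs of 4 vs 6, Levene's test was significant in 90 to 99% of trials across the distributions tried. With skewed data at the planned means and SD, a Shapiro test was significant in at least one arm in over 99%. If transition times are skewed, the rank test would usually become the primary test.

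**The case against.** The other side has several good points.

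- **No validity failure from the covariate rule.** A reader might infer that choosing covariates from the data produces false positives. It does not here: type I error under the rule was 0.034 to 0.048, and an unadjusted randomised comparison is unbiased. This stands, and the harm is efficiency. The planned n also already gives about 90% power where the article asks for 80%.
- **Chance imbalance.** A reader might treat a non-significant gestational age gap as bias. With an assumed SD of 1.6 weeks, the largest such gap is 1.96 × 1.6 × √(2/140) = 0.375 week. At an assumed 1 to 2 days per week, that is about 0.4 to 0.7 day. This is the extreme edge of the range, and the unadjusted SE already covers such imbalance, so it is not an additional harm.
- **The 19 to 20% rejection rate.** A reader might take it as the trial's false-positive rate. The article plans one common SD. If timing has no effect at all, the two distributions are identical and the rank test is valid. What remains is a mismatch between the test and the planned mean difference, which needs both skewness and unequal spread to matter.
- **The rank test can be the stronger test.** At the planned means with SD 4.99 in both arms, its power was 96% against 89% for Welch (lognormal) and 93% against 90% (gamma). With a constant coefficient of variation, both were 90%. Demoting it is not free.
- **Placement.** The covariate rule sits under additional analyses, and its reach over the primary comparison is ambiguous. However, it refers to the results without restriction. The optional regressions could include gestational age, but nothing commits to that, and a subgroup analysis does not adjust the overall estimate.

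That an unseen analysis plan may give more detail does not answer the point: both rules are fixed in this article.

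**Conclusion.** The point holds as one of efficiency and of matching the test to the planned quantity. The P<0.05 rule adjusts for gestational age in about 5% of trials and recovers little of the available gain: at r = 0.5, power is 0.908 under the rule against 0.960 with fixed adjustment. These figures rest on assumed correlations; the 5% follows from randomisation alone.

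The non-parametric fallback does not test the mean difference used for sample size. How much this matters depends on distributions that the article does not give: nothing at equal SDs, about 9% rejection at 4.5 vs 5.5 and about 19% at 4 vs 6 under lognormal data with equal means. The documents do not support a claim of general type I error inflation from either rule. This should be fixed, but it is not a defect that invalidates the trial.

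**What to change.** Delete the baseline P<0.05 rule. Pre-specify the primary analysis of transition time as a linear model with arm and gestational age at birth (continuous), heteroscedasticity-robust standard errors, and the difference in days with its 95% CI, whatever the baseline tests show. In unadjusted comparisons, replace the switch to a rank test under unequal variances with Welch's test. Report the rank test as a sensitivity analysis.

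Adjust the other continuous outcomes for gestational age as well. Do not add birth weight automatically: the Weight gain outcome already has it in its formula.

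The cost is a wording amendment, made before anyone sees outcome data by arm. Gestational age is already collected. The one small downside is that the rank test can have more power for skewed data under some alternatives; reporting it as a sensitivity analysis keeps that information.
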